## Abstract

**Background:**

Recuperative techniques have been used to anticipate and potentiate recovery. The massage is one of the most widely used in sports. Among the ways to demonstrate the recovery of the organism is the resumption of autonomic modulation of heart rate, which can be analyzed in situations that cause disturbances in the behavior of the cardiovascular system with the objective of verifying the responsiveness of the autonomic nervous system (ANS). Recovery can be assessed through heart rate variability (HRV) which analyzes the oscillations in consecutive heartbeats, thus allowing an important non-invasive alternative for the study of modulation of the ANS. The objective of the study will be to measure the effects of massage as a recuperative technique on the autonomic modulation of heart rate and cardiorespiratory parameters at different moments of application.

**Methods:**

This is a randomized, cross-over clinical trial. Forty men aged 18 to 30 years, healthy and physically active according to the International Physical Activity Questionnaire will participate in the study. Participants will be randomized into groups, which will perform the five interventions of the study at randomized moments, one intervention per session: Intervention 1: control; Intervention 2: participants will receive the massage protocol; Intervention 3: performance of the stress protocol; Intervention 4: participants will perform the stress protocol and immediately after receive the massage; Intervention 5: participants will perform the stress protocol and 1 h after conclusion of the protocol will receive the massage. The sessions will occur with an interval of 1 week between them and, due to the technique used, blinding participants and therapists is not possible. The primary outcome measure is HRV that will be measured 2 h after the conclusion of each intervention, and secondary outcome measures, which include heart rate, respiratory rate, blood pressure, oxygen saturation, and individual touch perception, will be measured at specific moments in the course of each intervention.

**Discussion:**

The implementation and use of this standardized protocol should provide important and reliable information regarding the use of massage in post-exercise recovery, with the identification of its effects on the ANS and the best timing and form of massage application. The data obtained in the present study will provide subsidies for the best management of application of the technique in sports clinical practice, considering periods of training and, mainly, of competitions.

**Trial registration:**

ClinicalTrials.gov, ID:NCT03094676. Pre-results. 12 March 2018.

**Electronic supplementary material:**

The online version of this article (10.1186/s13063-018-2830-1) contains supplementary material, which is available to authorized users.

## Background

Training in its simplest form represents acute challenges to the body intended to optimize chronic improvements in physiological capabilities [1]. The success of the processes of performance improvement and injury prevention depends on the quality of the transition between the physical training stimuli, in addition to the systematization of the exercise prescription. In this sense, an adequate recovery becomes an important aspect of any conditioning program, both for athletes, technicians, and for several health-related professionals [1].

Physical exercise can be a stressor mechanism to body systems, promoting several organic modifications, and recovery processes are commonly employed in the sense of restoring the systems to their basal condition [1]. To accelerate the recovery process after physical exercise, specific techniques are used, and early recovery is considered fundamental for performance, especially within the sporting scene [2]. Of these techniques, massage, consisting of the mechanical manipulation of the corporal tissues [2], stands out, being considered the most commonly used technique in the sports field, both in training and competition periods [3].

Clinical, functional, and metabolic modifications are already described in the relevant literature regarding the effectiveness of massage [4–9]. It is believed that the massage technique is beneficial in reducing muscle pain, by relieving muscle tension and edema as exposed by Hunter et al. [10], stimulating the metabolic clearance of blood lactate and creatine kinase as proposed by Smith et al. [11], and promoting improvement in flexibility and range of motion [6].

However, the physiological adaptations promoted by massage can also be monitored through autonomic nervous system (ANS) and cardiovascular responses [11]. Studies have shown that relaxing therapeutic modalities, such as massage, have presented favorable results for recovery in cardiovascular markers, such as a decrease in heart rate and blood pressure in the post-exercise period [12–14].

In relation to the markers of autonomic recovery, massage has also demonstrated positive results in the recovery capacity. Arroyo-Morales et al. [15] performed a 40-min massage on the whole body of the participants after a three-sprint Wingate exercise protocol of 30 s separated by a 3-min interval and observed that massage was favorable for the recovery of the heart rate variability (HRV) indices to baseline.

However, in the study of Arroyo-Morales et al. [15] some gaps can be identified in the literature. Before the massage technique, the participants performed 15 min of active and passive recovery, the massage technique had five different modalities of tissue manipulation applied in regions that were not protagonists during the stress, with prolonged duration and applied only at one moment. These details in the design of the study may influence the responses found in the recovery of autonomic modulation of heart rate, especially considering practical applications. However, the main gap addressed by the present study protocol is related to the moment of application of massage as a recuperative technique. To study the optimal timing of the technique seems interesting since various sports modalities participate in several competitions throughout the day and, thus, it is necessary to understand the best moment of application of the recuperative technique to guarantee the best performance of the athletes.

The recovery of autonomic modulation of heart rate has been considered an important global marker of athlete recovery. Ihsan et al. [16] reported that the return of HRV values is a good indicator for exercise dynamics to be applied in training or in competitions. In addition, although massage is widely used as a recuperative technique, there are gaps in the literature regarding the effectiveness of massage in the autonomic modulation of heart rate and cardiorespiratory parameters; and especially in relation to the best moment of application. It is unclear whether performance of the massage technique has a beneficial effect on HRV both to anticipate its recovery and potentiate the effects of recovery depending on the moment of its application.

The present study is a randomized clinical trial aimed at investigating the effects of massage as a recuperative technique on the recovery of autonomic modulation of heart rate and cardiorespiratory parameters in physically active young people comparing two distinct scenarios: (1) immediately after stress in order to investigate if the technique anticipates the recovery of the ANS, and (2) immediately after the recovery moment of the ANS in order to investigate whether the technique potentiates the recovery of the ANS.

## Methods

### Study design

A randomized, cross-over, controlled clinical trial will be conducted at the Center for Studies and Care in Physiotherapy and Rehabilitation of the Universidade Estadual Paulista (FCT/UNESP), Presidente Prudente, São Paulo, Brazil. The study design is illustrated in Fig. 1. The study protocol follows the SPIRIT 2013 Checklist (Standard Protocol Items: Recommendations for International Trials) (Additional file 1) and TIDieR (Template for Intervention Description and Replication) so that the information and quality of the reports of the interventions are well described. The trial was registered at ClinicalTrials.gov (NCT03094676).

**Fig. 1 Fig1:**
[figure not shown]
Study design. Legend: ● individual touch perception; ■ heart rate variability (HRV); ▲ cardiorespiratory parameters

### Participants

A total of 40 participants will be recruited at the local university (Universidade Estadual Paulista) through online advertising and approaching participants by telephone, SMS, and social networks, from January 2018 to April 2018. Participants will be considered eligible if they are apparently healthy, male, aged between 18 and 30 years, and have a Body Mass Index (BMI) classified as normal (between 18.5 and 25 kg.m^2^) according to the World Health Organization [17]. In addition, participants who have at least one of the following characteristics will not be included: smokers, use of medications that influence autonomic modulation of heart rate, alcoholics, known metabolic and/or endocrine disorders, individuals with musculotendinous injuries in the region of the lower limbs and trunk in the previous 6 months, and sedentary, insufficiently active, and very active individuals according to the International Physical Activity Questionnaire (IPAQ) [18]. With the exception of assessing the level of physical activity that will be carried out through the application of the IPAQ, the principal investigator will determine whether potential participants meet the eligibility criteria during an initial interview. Ethical approval has been granted by the Human Ethics Committee of the São Paulo State University (CAAE: 57584116.6.0000.5402).

### Analysis population

The criteria that define the exclusion of the participant in the final analysis of the data will be: intercurrences during the execution of the protocols that prevent their continuity, absence from more than 80% of the proposed sessions, and capture errors in the RR intervals.

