### Design description

The study will be conducted in five interventions (Intervention 1 (I1); Intervention 2 (I2); Intervention 3 (I3); Intervention 4 (I4); Intervention 5 (I5)), and the groups will be randomized to perform these interventions at several moments, with a 1-week interval between interventions. Data collection will always be performed at the same period of day and in air-conditioned environments.

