#### Primary outcome

HRV will be used as the primary outcome as it is an important overall marker of post-exercise recovery [16]. The HRV analysis will be performed from the series of RR intervals captured by the cardiofrequency meter Polar Electro Oy – model V800, and linear methods analyzed in the time domain and frequency domain, and Poincaré plot. All HRV indices will be obtained through the *software* Kubios HRV – version 2.0 [20].

For this analysis, the time series of RR intervals will initially be subjected to digital filtering using the *software* Kubios HRV – version 2.0, supplemented by manual filtering, to eliminate premature ectopic beats and artifacts, and only series with more than 95% of sinus beats will be included in the study [20]. Through visual analysis of the time series, the absence of ectopic artifacts or beats that can interfere in the HRV analysis will be observed.

During the recovery period, the evaluated moments will be: R1 (initial 5 min of rest before performing the interventions), R2 (initial 5 min of recovery), R3 (fifth to 10th minutes of recovery), R4 (10th to 15th minutes of recovery), R5 (20th to 25th minutes of recovery), R6 (30th to 35th minutes of recovery), R7 (40th to 45th minutes of recovery), R8 (50th to 55th minutes of recovery), R9 (60th to 65th minutes of recovery), R10 (70th to 75th minutes of recovery), R11 (90th to 95th minutes of recovery), and R12 (115th to 120th minutes of recovery). It is worth mentioning that 256 consecutive RR intervals will be obtained at these moments [21].

HRV indices in the time domain (rMSSD and SDNN), frequency domain (low-frequency spectral component (LF) and high-frequency spectral component (HF)), and the Poincaré plot (SD1 and SD2) will be evaluated [22].

In the time domain, the rMSSD Index corresponds to the square root of the square mean of the differences between the adjacent normal RR intervals in a time interval expressed in milliseconds and evaluates the behavior of the parasympathetic autonomic modulation [22], while the SDNN Index represents the standard deviation of all normal RR intervals recorded in a time interval, expressed in milliseconds, and is considered a measure of global variability, that is, it evaluates both sympathetic and parasympathetic modulation [22].

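### With five sessions the 80% absence rule excludes only men who attended none, and the participant-level RR exclusion conflicts with the series-level 95% sinus-beat rule

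*Protocol article*

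**What the plan says.** The Analysis population section opens with "The criteria that define the exclusion of the participant in the final analysis of the data will be" and lists three criteria. The first is "intercurrences during the execution of the protocols that prevent their continuity". The second and third are "absence from more than 80% of the proposed sessions, and capture errors in the RR intervals".

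All three act on the participant. The third carries no threshold.

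The number of sessions is fixed elsewhere. Design description states "The study will be conducted in five interventions", and the Methods part of the abstract describes groups "which will perform the five interventions of the study at randomized moments, one intervention per session".

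The Primary outcome section treats RR quality differently. The RR series is filtered digitally and then by hand, after which "only series with more than 95% of sinus beats will be included in the study". It lists twelve HRV moments per session, R1 to R12.

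The Statistical analysis section plans ANCOVA adjusted for baseline, repeated-measures ANOVA or Friedman across moments, and one-way ANOVA or Kruskal-Wallis across groups. It names no mixed model.

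**The concern.** These rules decide who is analysed for the primary outcome, and two of them do not work as stated.

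The attendance rule has no practical effect. The comparisons of interest under Study interventions are massage immediately after stress (I4) against massage one hour after stress (I5), with stress alone (I3) as the natural reference. A man with one session informs none of these within himself. He still passes the rule, and in one-way ANOVA or Kruskal-Wallis his single session would count as unpaired information in one intervention's results.

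The RR rule leaves open whether a failed recording costs a window, a session or the man. Read literally, Analysis population removes the man from the whole final analysis. That would discard his other usable RR recordings. It would also discard his blood pressure, respiratory rate and oxygen saturation, which the Secondary outcomes section measures by other means (sphygmomanometer, counting and pulse oximeter). Two analysts could apply the text in good faith and analyse different sets of men.

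**Working it through.** **1. Attendance rule.** Inputs: 5 sessions (abstract; Design description) and exclusion if absence exceeds 80% (Analysis population). The cut-off is 0.80 × 5 = 4 sessions, so exclusion needs more than 4 absences.

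| Sessions missed | Absence | Above 80%? | Sessions attended |
|---|---|---|---|
| 0 | 0% | no | 5 |
| 1 | 20% | no | 4 |
| 2 | 40% | no | 3 |
| 3 | 60% | no | 2 |
| 4 | 80% | no (equal) | 1 |
| 5 | 100% | yes | 0 |

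Only the last row is excluded, and that man has no session data to exclude. This step needs no assumption.

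**2. RR rules side by side.**

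| | Analysis population | Primary outcome |
|---|---|---|
| Unit removed | participant | series |
| Threshold | none given | more than 95% sinus beats |
| Artefact filtering first | not mentioned | digital and manual |
| Scope | final analysis of the data | HRV analysis |

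Unit and threshold both differ.

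**3. The plan's tolerance for loss.** Sample size gives an effect of 26.9, SD 38.8, two-sided 5% and 80% power. The usual two-group formula reproduces the stated figure: 2 × [38.8 × (1.960 + 0.842) / 26.9]² = 32.66, rounded up to 33. The 10% allowance gives 33 × 1.10 = 36.3, stated as 36. Four more men are added because there are other HRV indices and no comparable trials, giving 40. Here 33 serves only as the plan's own stated requirement. The tolerated loss is (40 − 33)/40 = 17.5%.

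**4. Possible loss if one failed unit removes the man.** The documents give no failure rate, so q is an assumption, taken as independent between units. The share of men lost is 1 − (1 − q)^m. If the unit is each listed window, m = 5 × 12 = 60. If it is each session recording, m = 5.

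| q (assumed) | Lost, m = 60 | Left of 40 | Lost, m = 5 | Left of 40 |
|---|---|---|---|---|
| 0.1% | 5.8% | 37.7 | 0.5% | 39.8 |
| 0.5% | 26% | 29.6 | 2.5% | 39.0 |
| 1% | 45% | 21.9 | 4.9% | 38.0 |
| 2% | 70% | 11.9 | 9.6% | 36.2 |

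The rate at which 40 men fall to 33 is q = 1 − (33/40)^(1/m). This is 0.32% per window for m = 60, and 1 − 0.825^0.2 = 3.8% per recording for m = 5.

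**The case against.** The best defence reads the two RR passages together: isolated errors are filtered, a series with up to 5% non-sinus beats is tolerated, and only a gross recording failure counts as a capture error. A reader might infer that any single RR error removes a man and wastes up to 59 good windows. The text does not say so; the word 'any' is not there. This part of the defence stands, and what remains is a conflict over unit and threshold.

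The size of the loss is also open. The larger percentages need the window as unit, a failure rate the documents do not supply, and independence. For a given rate, failures that cluster within a man or a session would affect fewer men. The filtering step precedes the list of windows, so 'series' may mean the session recording; the assumed rates then lose under 10%. Nor is the allowance a fall from 40 to 36: the 10% takes 33 to 36, and the last four men were added for another reason.

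A reader might further infer bias that depends on the intervention, since three of the five sessions include the stress protocol. The documents do not show that recordings fail more often there. Removing a man also removes him from all five interventions, so their comparison stays balanced. The cost shown is in precision and representativeness. The criterion on intercurrences is limited to those that prevent continuation and is close to discontinuation.

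On attendance, one can say that a near-void rule harms nobody, and that keeping every man with some data is good practice. That holds under a model which weights a one-session man properly. It does not hold for the unpaired tests planned, and it does not make the stated threshold a working rule.

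**Conclusion.** The point holds in two parts. First, the attendance threshold cannot act as one: with five sessions it excludes only non-attenders. This is exact. The figure might be an inverted attendance requirement, but the document does not say so and that should not be presumed. Second, Analysis population and Primary outcome conflict on whether an RR failure removes the man or the series, and on the threshold.

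The consequence of the second part cannot be sized from the documents. For assumed independent rates of 0.5 to 2%, it runs from 2.5% of men (session recordings, lowest rate) to 70% (windows, highest rate), against a tolerated 17.5%. These figures show that the choice of unit matters; they do not predict the loss. The correction is moderate, and neither bias nor loss of power is demonstrated.

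**What to change.** 1. Delete the 80% threshold, or restate it as a number of sessions, for example as a requirement for usable data in the sessions being contrasted (I3, I4 and I5).
2. Reconcile Analysis population with Primary outcome: an RR failure under the 95% sinus-beat rule removes only the affected series, not the participant and not the non-RR outcomes. State whether a series is a window or a session recording.
3. Keep men with partial data wherever the model allows it. Classical repeated-measures ANOVA and Friedman need complete rows, so editing the exclusion list alone would not achieve this. A mixed model with a participant effect should replace the tests in the Statistical analysis section. If the threshold is simply deleted, a one-session man may then stay in, because the model gives him only the weight his data carry.

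Items 1 and 2 cost a few sentences, and item 3 a little more analysis work. No new data are needed. The rules should be settled before results are seen.

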### Randomization

Participants who meet the eligibility criteria and sign the consent form will be randomized, using simple randomization, for logistic reasons into five groups and the groups will be randomized into the different interventions of the study to determine the order of accomplishment. In order to guarantee the hidden allocation of the participants in the groups and the randomization of the study interventions, a researcher not involved in the recruitment will be responsible for this procedure using electronic software (Microsoft Office Excel). This researcher will be instructed not to previously inform the participants or other researchers about the procedures that will be performed in each session. The following figure presents the schematization of the aforementioned randomization processes (Fig. 2).

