### Sample size

As described above the primary outcome will be the HRV. The sample size calculation was carried out based on the study of Arroyo-Morales et al. [15] in which the SDNN Index of the HRV was selected, since it is an index that expresses the behavior of the ANS in a global way. To establish the sample size, a mean effect of 26.9 and standard deviation of 38.8 were chosen. The level of significance for the sample size is 5%, the power test is 80%, two-tailed test, and 10% of the total value of *n* is added to statistically supply the analyses in the case of withdrawals during data collection. The value obtained for the sample size was 33 participants, adding the 10% gave a sample of 36 volunteers. However, there are other indices besides the SDNN Index within the HRV, and this situation generates an environment where the sample size could be underestimated. In the same sense, due to the new proposal presented by the study, there are no trials in the literature that have the same proposal dynamics, and thus, for safety we will add four volunteers to ensure the statistical analysis of all HRV indices, thus totaling a sample of 40 participants.

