### Statistical analysis

For analysis of the data of the population profile, the descriptive statistical method will be used and the results presented as values of means, standard deviations, median, minimum and maximum numbers, and confidence interval. The normality of the data will be evaluated through the Shapiro-Wilk test.

The comparisons of cardiorespiratory parameters and HRV indices between interventions (I1, I2, I3, I4, and I5) and moments (rest (R1) vs recovery moments (R2–R12)), the data are analyzed from the prism of the covariance analysis (ANCOVA), which will be adjusted for the baseline value of the evaluated variable and generated estimated means after such adjustment (extracting the variance explained by the confounding variables). The Levene test will be used to prove the homogeneity of the variances at the created moments, and the Bonferroni post hoc test will be used for comparison. To guarantee homogeneity of data the variable can will be transformed into logarithm.

For analysis of the moments (rest vs recovery moments), repeated measures ANOVA with the Tukey post test for parametric distribution or Friedman test with Dunnett’s post test for non-parametric distribution will be used and the analysis of the different groups will be performed by means of one-way ANOVA with the Tukey post test or the Kruskal-Wallis test with Dunnett’s post test.

The level of significance will be *p* < 0.05 for all tests. The SPSS statistical program (version 13.0) (SPSS Inc., Chicago, IL, USA) will be used for the analyses. Data integrity will be monitored by regularly scrutinizing data files for omissions and errors. Participants will be given an anonymous study ID to protect confidentiality, and only study investigators will have access to the final trial data set.

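### Simple randomisation into five order-groups, with no stated position-balanced set of orders, leaves interventions partly non-orthogonal to session, and the stated ANCOVA does not adjust for session

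*Protocol article*

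**What the plan says.** The trial is a five-session cross-over. The abstract describes groups "which will perform the five interventions of the study at randomized moments, one intervention per session". Order is set in two steps in the Randomization section: participants "will be randomized, using simple randomization, for logistic reasons into five groups and the groups will be randomized into the different interventions", and the second step fixes the order in which each group does them. The Design description repeats that "the groups will be randomized to perform these interventions at several moments, with a 1-week interval between interventions". The Sample size section ends "thus totaling a sample of 40 participants".

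The text gives no group size, no blocking and no rule for which five orders are used. It refers to Fig. 2 for the scheme; that figure was not available for this review.

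The Statistical analysis section compares interventions and moments by ANCOVA, "which will be adjusted for the baseline value of the evaluated variable and generated estimated means after such adjustment". It adds repeated-measures and one-way ANOVA, or rank tests in their place. It names no session, period or sequence term.

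**The concern.** A cross-over removes differences between men. It removes differences between sessions only if each intervention falls equally often in each session, or if session is in the model.

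Here order is set for whole groups, so 40 men share at most five orders, and the group sizes are left to chance. Three of the five weekly sessions (I3, I4 and I5) include 100 jumps followed by a Wingate test. Habituation or a training response from session to session is therefore plausible. If the recovery response drifts in this way and the analysis ignores it, part of the drift enters the contrasts among I3, I4 and I5. I4 against I5 is the comparison on which the timing question rests.

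**Working it through.** **Inputs.** 40 men (Sample size); simple randomisation into five groups with order set by group (Randomization); five interventions, one per session (abstract); planned SDNN effect from "a mean effect of 26.9 and standard deviation of 38.8 were chosen" (Sample size).

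**The plan's own figure.** The documents give no figure for group size or session balance. The stated sample size does reproduce with the two-group, per-group formula: 2 × (1.96 + 0.84)² × 38.8² / 26.9² ≈ 33, and 33 × 1.1 = 36.3. The present point does not depend on it; 26.9 serves below only as a yardstick.

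**Step 1: group sizes.** Sizes are multinomial (40; 1/5 each).
- P(all five groups = 8) = 40! / (8!⁵ × 5⁴⁰) = 0.00084.
- SD of one group's size = √(40 × 0.2 × 0.8) = 2.53.
- In 1,000,000 simulated draws the mean smallest group was 4.9 and the mean largest 11.4. The mean difference was 6.5, and it was 5 or more in 79% of draws.

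**Step 2: gap in mean session between two interventions.** In a random order of five, one position has variance 2 and two positions have covariance −0.5. The difference between two positions therefore has variance 2 + 2 + 1 = 5.

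| Orders (assumed) | Group sizes | Variance of the gap | SD (sessions) |
|---|---|---|---|
| Latin square | 8 each | 0 | 0 |
| Latin square | by chance | 5/40 = 0.125 (average over pairs) | 0.35 |
| Drawn independently | 8 each | 5 × (1/5) = 1.00 | 1.00 |
| Drawn independently | by chance | 5 × 0.22 = 1.10 | 1.05 |

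The factor 0.22 is the expected sum of squared group shares: 5 × (64 + 6.4) / 40² = 352/1600.

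Simulation agrees. The absolute I4–I5 gap has median 0.25 and 95th percentile 0.75 sessions in the second row, and 0.75 and 2.0 in the fourth. Five independently drawn orders form a Latin square with probability 161280/120⁵ = 6.5 × 10⁻⁶.

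**Step 3: shift in I4 minus I5.** For a linear drift of *d* ms SDNN per session that the analysis does not remove, the 95% range is ±1.96 × SD × *d*. The documents give no drift, so *d* is an assumption.

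| *d* (ms per session) | Latin square, chance sizes | Independent orders, chance sizes |
|---|---|---|
| 0 | 0 | 0 |
| 1 | ±0.7 ms | ±2.1 ms |
| 2.5 | ±1.7 ms (6% of 26.9) | ±5.1 ms (19% of 26.9) |

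**Step 4: cost of adding session to the model.** With participant and session effects fitted and group sizes left to chance, the simulated mean efficiency for I4 minus I5, relative to a balanced design, is about 97% under a Latin square (5th percentile 94%). With independent orders it is about 74% (5th percentile 43%).

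**The case against.** The strongest reply is that the larger figures rest on an assumption about the orders that the text does not settle. Five groups and five interventions are compatible with one group per intervention each week, which is a Latin square, and Fig. 2 may show exactly that. In that case the SD of 0.35 equals √(5/40), the value for 40 men each given his own random order. A reader might infer that five orders make chance imbalance much worse than 40 men would suggest. That is so only if the orders are drawn independently. This part of the reply stands.

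A reader might also infer that intervention is confounded with session. The documents do not support that. Every man is to receive all five interventions and the imbalance is random, so this is partial, chance non-orthogonality. It does harm only if a session effect exists and is left unadjusted.

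Nor should simple randomisation carry all the blame: with independent orders, equal groups lower the SD only from 1.05 to 1.00.

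The ANCOVA also gives some protection. R1 is the rest period before the intervention. If it is recorded at every session, as the Study interventions and Primary outcome sections suggest, adjustment for it takes out at least part of any trend in resting SDNN. What mainly remains is drift in the response to stress and massage.

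Finally, a condensed article may leave a session term to the analysis plan, so its absence is weak evidence that none is intended. What survives is that simple randomisation is stated outright. It almost surely leaves session position unbalanced under either reading of the orders, and the adjustment that is stated is for baseline value alone.

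**Conclusion.** The point holds as a cheap improvement to a stated method; it does not show that the trial's contrasts are invalid. Equal groups have probability 0.0008. The SD of the I4–I5 gap lies between about 0.35 sessions (Latin square) and 1.05 sessions (independent orders). The choice of orders is the main cause and group size the lesser one.

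The resulting 95% range of shift is about ±0.7 to ±2.1 ms per 1 ms of drift per session, less whatever the session baseline absorbs. This assumes a linear drift in the recovery response. A reader might take a share such as 19% of the planned effect as the expected bias. That figure needs both independently drawn orders and a drift of 2.5 ms per session, and the documents establish neither.

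**What to change.** Keep the five logistic groups, but assign them the rows of a 5×5 Latin square and state this in the text. If Fig. 2 already shows such a square, saying so is enough for this part. For men not yet randomised, use blocked allocation aiming at 8 per row. Equal groups without balanced orders would not solve the problem. For everyone, include session (1–5) as a fixed effect in a within-participant model.

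The cost is a new list from the researcher who already does the randomisation, four degrees of freedom, and about 3% of efficiency under a Latin square.

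Re-allocation may reach few men. Recruitment is under way, and the Trial status section gives 35 days from start (9 April 2018) to primary completion (14 May 2018), while five weekly sessions span at least 28. On those dates nearly all men would start in the first week. If allocation is already complete, add the session term and report the realised orders and group sizes.
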